### 2.8. Data Collection

Data collection is being conducted in groups of up to 12 participants with trained study personnel. Paper questionnaires are given to the participants. All literate participants are asked to fill out the questionnaires on their own. For those with reading difficulties, the questions are read aloud, and the response options are explained. The study personnel are trained not to influence the answers. All participants sit as far from each other as is necessary to safeguard their anonymity. All participants are informed that no one (i.e., including their parents, friends, or any government or nongovernment organization) apart from ClimbAID will be given information about their answers. The trained study personnel have the same cultural background (Syrian or Lebanese) as the participants to reduce misunderstandings due to different Arabic dialects. Complete data collection is also planned for dropouts, if available.

### 2.9. Measures

#### 2.9.1. Primary Outcome Measure

Overall mental well-being is measured with the Arabic version of the WEMWBS (Warwick-Edinburgh Mental Well-Being Scale) at both time points of the study. The WEMWBS consists of 14 items covering the emotional and functional aspects of mental well-being. Sum scores range from 14 to 70 with higher scores indicating higher overall mental well-being. An improvement of 3 to 8 points is regarded as clinically relevant [44]. 

#### 2.9.2. Secondary Outcome Measure

Psychological distress is measured with the Arabic version of the K-6 Distress Scale [49,50]. The K-6 consists of six items covering the main depressive symptoms (i.e., hopelessness, feeling worthless, nervous, so sad that nothing can cheer me up, and the feeling that everything is an effort). Sum scores range from 6 to 30 with higher scores signifying higher psychological distress. The authors of the Arabic validation study used 16.25 as the cut-off score for psychological disorders.

Self-efficacy is measured with the Arabic version of the general self-efficacy scale (GSE) [51]. The GSE measures optimistic self-beliefs about coping with a variety of difficult demands in life. Its 10 items can be rated on a 4-point scale ranging from 1 (not at all true) to four (exactly true). The total score ranges from 10 to 40 with higher scores indicating higher self-efficacy. The GSE has good psychometric properties [52].

Social cohesion is measured with a five-item set and an additional single-item measure from the ARK Regular Perception Survey. This survey is used specifically to analyze social tension throughout Lebanon. The items were modified to fit the situation experienced by adolescents. The five-item set uses a 5-point Likert scale ranging from 1 (very disagreeable) to 5 (very agreeable) to ask how agreeable five different scenarios are. The questions always refer to members of the other nationality, and the scenarios involve playing with or attending school with children of the other nationality, living next door to or sharing a workplace with a member of the other nationality, or having a family member who marries someone of the other nationality. In the additional single-item measure, participants are asked to rate how much they agree with the phrase: “Lebanese and Syrians share many values and have compatible lifestyles” on a 4-point Likert scale ranging from 1 (strongly agree) to 4 (strongly disagree) [5]. 

The following variables are recorded as possible variables of influence or confounding variables in the questionnaire format:Sociodemographic data: sex, age, school enrollment, nationality, living conditionsPhysical activityMedical conditionsClimbing experience

In addition, qualitative data are being gathered from at least 30 participants in the intervention groups. The sample is balanced according to age and sex, and participation is voluntary. These data are being collected via semi-structured qualitative interviews by trained personnel who are not involved in the intervention to investigate the acceptance and factors that affect the climbing program. The interview guidelines focus on the categories Reach, Effectiveness, and parts of the implementation according to the RE-AIM scheme by Holtrop et al. [53]. It is divided into main questions, possible follow-up questions, and probes. The main questions are: Reach: “Can you tell us how it came about that you are now participating in the YouCLIMB Program?” Effectiveness: “Can you tell us about your experience with the YouCLIMB program?” Implementation: “Were there any barriers that prevented you from participating or that made participating difficult?” Closing question: “Is there anything else you want to tell me?”

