## 2. Methods

### 2.1. Overall Aims

The aim of the study is to test the effectiveness of a climbing intervention among adolescent locals and refugees living in the Bekaa region of Lebanon. We hypothesized that the climbing intervention will have a beneficial effect on participants’ psychological well-being. Additionally, we are investigating the impact of the intervention on, and the relationships between, self-efficacy, psychological distress, participants’ perceptions of other nationalities (Syrian, Lebanese, Palestinian), and social cohesion.

To gain insight into the modes of action and potential benefits that are specific to culture and living conditions as well as barriers and facilitators of the intervention, we are conducting qualitative interviews with a subsample of participants, balanced for age, sex, and intervention subgroup.

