### 2.11. Data Analysis

#### 2.11.1. Quantitative Data

The data analyses will be performed with the “IBM SPSS Statistics 28” software. To assess the quality of the group allocation, the baseline data from the intervention and control groups will be examined for statistically significant differences. All data will be investigated for plausibility. Participants who drop out of the study but are still available for the posttest will be interviewed subsequently. A missing data evaluation will be carried out, and missing values will be imputed with EM-Imputation [54]. The primary data analytic strategy will be “per protocol”. As a sensitivity analysis, an additional analysis with “intention to treat” will be performed. The level of statistical significance will be set at *p* ≤ 0.05. Mixed ANOVAs (time × group) will be used to determine differences between the groups. Additionally, regression analyses will be used to test the hypotheses and check for possible confounders. Differences between groups will be determined before analysis, and if there are significant differences in important sociodemographic variables, appropriate statistical methods (e.g., propensity score matching) will be used. Secondary outcomes will be tested in an exploratory fashion with *t* tests for independent samples.

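### As described, the social cohesion items do not cover the three-nationality aim, and the planned t test for the five-item score ignores the respondent's nationality

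*Protocol article*

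**What the plan says.** Section 2.1 (Overall Aims) lists among the things to be studied participants' "perceptions of other nationalities (Syrian, Lebanese, Palestinian), and social cohesion".

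Section 2.9.2 describes two measures under social cohesion. The first is a set of five scenarios, of which the article says: "The questions always refer to members of the other nationality". They are rated on a "5-point Likert scale ranging from 1 (very disagreeable) to 5 (very agreeable". The second is an additional single item, "Lebanese and Syrians share many values and have compatible lifestyles", rated on a "4-point Likert scale ranging from 1 (strongly agree) to 4 (strongly disagree". The section does not say which nationality is the other one for a given respondent. It does list nationality among the recorded possible confounders.

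Section 2.11.1 states that "Secondary outcomes will be tested in an exploratory fashion", using independent-samples t tests. It also plans a baseline comparison of the arms, regression analyses to test the hypotheses and check confounders, and methods such as propensity score matching if important sociodemographic variables differ significantly.

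**The concern.** There are two linked problems.

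First, the aim names three nationalities, but no quantitative measure in the article is described as asking about Palestinians. An analysis plan cannot supply an item that was not asked, so this mismatch does not depend on documents that are not shown.

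Second, on the natural reading, a Lebanese adolescent's five-item score is an attitude toward Syrians, and a Syrian adolescent's is an attitude toward Lebanese. The Introduction describes worsening relations between these two communities, so equal average scores in the two directions cannot be taken for granted. Comparing arms without nationality assumes in effect that the mix of respondents is the same in both arms. Section 2.6 gives reason for doubt: some participants choose their cycle, and accompanied participants are placed with relatives, who will often share a nationality. A difference in who answered could then be read as an effect of climbing on cohesion.

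**Working it through.** The plan gives no figure for this outcome, so there is none to reproduce. The check compares the sections and adds an illustration.

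**Aim against instrument**

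- Aim (2.1): Syrian, Lebanese, Palestinian.
- Five items (2.9.2): one other nationality, in the singular and not named.
- Single item (2.9.2): Lebanese and Syrians only.
- Eligibility (2.3): refugees and host community, with no limit by nationality, so Palestinians may enrol.
- Data collection (2.8): the staff's shared background with participants is given as Syrian or Lebanese, which fits a two-nationality study better than the stated aim.

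**Would the planned adjustment pick up a nationality imbalance?**

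Inputs: 52 per arm at posttest and 80 per arm enrolled (2.7); significance at 0.05 (2.11.1). A 50:50 Lebanese-Syrian mix is assumed, because the article gives none.

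- SE of the difference in proportions at 52 per arm: sqrt(2 × 0.25 / 52) = 0.098. Smallest significant difference: 1.96 × 0.098 = 0.19, or about 19 points.
- At 80 per arm: sqrt(2 × 0.25 / 80) = 0.079, and 1.96 × 0.079 = 0.155, or about 15 points.

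Smaller imbalances would leave the t test unadjusted under the stated rule.

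**What could such an imbalance do to a posttest comparison?**

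Shift = (gap between host and refugee scores, in within-nationality SD) × (difference in mix). The gap of 0.5 to 1.0 SD and the imbalance of 10 to 20 points are assumptions.

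- Low end: 0.5 × 0.10 = 0.05 SD.
- High end: 1.0 × 0.20 = 0.20 SD.

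Mixing the two targets also adds variance of p(1 − p) × gap²: 0.25 × 0.5² = 0.0625 to 0.25 × 1.0² = 0.25. A standardised effect is multiplied by 1/sqrt(1.0625) = 0.97 to 1/sqrt(1.25) = 0.89, a loss of 3 to 11%.

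**Can the two directions be tested separately?**

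At a 50:50 mix each direction has about 52 × 0.5 = 26 per arm, half of what 2.7 requires for the primary comparison. Separate results can only be descriptive.

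**The case against.** The strongest reply is that the plan already deals with nationality. It is recorded as a possible confounder, the arms are compared at baseline, regression is planned, and matching is available. This stands in part. However, the named test for secondary outcomes is the t test, the hypothesis stated in 2.1 concerns psychological well-being, and matching depends on a significant difference. Nothing guarantees that nationality enters the cohesion analysis.

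The size of the shift can also be challenged, and much of that challenge stands. The 0.5 to 1.0 SD gap has no source in the article. Both arms are measured at baseline and after the intervention, and 2.11.1 does not say whether the t tests use posttest or change scores; on change scores a stable gap cancels. Chance imbalance among randomised participants is not bias, since the standard error covers it. Section 2.6 puts applicants limited to one cycle at about 20%. If they split evenly between arms, they alone produce a 10-point imbalance only if the two arms' self-selectors differ by 50 points in nationality (0.20 × 0.50 = 0.10). Family placement could add to this, but no figure is given.

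It is also fair to say that willingness to live alongside the other group is a coherent attitude whichever side answers. Pooling is therefore defensible, provided nationality is accounted for.

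Finally, the questionnaire is not shown and may define the target for each respondent. If so, the article needs only to say it.

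A reader might go further and infer that all six items are added up and tested once, so that the opposite scoring directions cancel part of any benefit. The article does not support this. It presents the single item as additional, on its own range, states no combined score, and speaks of t tests in the plural. The anchors make each direction readable, and two measures scored in opposite directions do no harm when analysed separately.

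**Conclusion.** The point holds in two parts. The aim in 2.1 and the instrument in 2.9.2 do not match on Palestinians: as described, there is no separate measure of attitudes toward them and no defined target for a Palestinian respondent. In addition, the five-item score changes meaning with the respondent's nationality, while the stated test leaves nationality out unless a significant baseline difference is found. That rule would miss imbalances below about 19 points at 52 per arm, or about 15 points at 80, for a 50:50 mix.

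The shift of 0.05 to 0.20 SD is an illustration. It rests on the assumed gap and imbalance and applies to posttest comparisons only. It does not show that the trial is biased. Because the outcome is secondary and exploratory, the consequence is limited to how a social cohesion result may be read. The scoring direction of the single item is only a reporting detail.

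**What to change.** - In 2.11.1, replace the t test for the five-item score with a linear model containing arm and respondent nationality, whether or not the arms differ significantly at baseline.
- Show Lebanese-to-Syrian and Syrian-to-Lebanese results descriptively, without separate tests.
- In 2.1, narrow the aim to Lebanese-Syrian attitudes. If the questionnaire does cover Palestinians, state in 2.9.2 the target used for each respondent group instead.
- Report the single item separately from the five items, and state that higher values mean less agreement.

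Nationality is already recorded, so no new data are needed and the cost is a few sentences. The real concession is giving up the aim concerning Palestinians if the items do not support it. Table 1 gives recruitment as complete, so this is more realistic than adding items.

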### 2.10. Data Quality Management

All data collectors and qualitative interviewers, as well as the facilitators are thoroughly trained for their respective tasks by the study headquarter and the ClimbAID organization. Treatment adherence is documented with detailed session protocols. 

Quantitative data and all identifiable data remain within the ClimbAID organization. Only members of ClimbAID have access to the lists of the participants’ names and codes. All analyses are conducted on pseudonymized data. Published material will not contain any patient-identifying information.

### 2.11. Data Analysis

#### 2.11.1. Quantitative Data

The data analyses will be performed with the “IBM SPSS Statistics 28” software. To assess the quality of the group allocation, the baseline data from the intervention and control groups will be examined for statistically significant differences. All data will be investigated for plausibility. Participants who drop out of the study but are still available for the posttest will be interviewed subsequently. A missing data evaluation will be carried out, and missing values will be imputed with EM-Imputation [54]. The primary data analytic strategy will be “per protocol”. As a sensitivity analysis, an additional analysis with “intention to treat” will be performed. The level of statistical significance will be set at *p* ≤ 0.05. Mixed ANOVAs (time × group) will be used to determine differences between the groups. Additionally, regression analyses will be used to test the hypotheses and check for possible confounders. Differences between groups will be determined before analysis, and if there are significant differences in important sociodemographic variables, appropriate statistical methods (e.g., propensity score matching) will be used. Secondary outcomes will be tested in an exploratory fashion with *t* tests for independent samples.

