### 2.7. Sample Size Estimation

Power calculation was performed using G*Power software [48] (University of Duesseldorf, Germany) with a two-tailed alpha of 0.05, a beta of 90%, and an estimated effect size of Cohen’s d = 0.55. This resulted in a necessary sample (as treated AT) of at least 52 members per group at posttest. 

As the dropout rate is difficult to foresee in the current political and economic situation, we assumed a drop-out rate of 35% per intervention cycle. Thus, we need to enroll 80 participants in the IG and the CG, respectively. Hence, at least 160 adolescents need to be included in the study, distributed across the six climbing groups (each consisting of 12–14 participants) and the control group. Including the waitlist-control group (which will be offered the intervention after the study period), up to a total of 160 adolescents should thus be provided with a climbing program. Figure 2 gives an estimated overview about sample sizes.

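### EM imputation with no allowance for imputation uncertainty makes the intention-to-treat sensitivity analysis unreliable, to a degree set by the share of missing posttests

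*Protocol article*

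**What the plan says.** Section 2.11.1 (Quantitative Data) of the protocol article commits to a missing-data evaluation, after which "missing values will be imputed with EM-Imputation [54". The tests that follow are standard: "Mixed ANOVAs (time × group) will be used to determine differences between the groups", regression analyses, and independent-samples t tests for the secondary outcomes. Per protocol is the primary strategy, and "As a sensitivity analysis, an additional analysis with “intention to treat” will be performed". The section mentions no repeated imputations, pooling or variance adjustment. It does not say whether group enters the EM model, or whether imputation is confined to one analysis set.

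Section 2.7 (Sample Size Estimation) shows how much could be missing: "we assumed a drop-out rate of 35% per intervention cycle", with 80 enrolled per group so as to have "at least 52 members per group at posttest".

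Two places limit the loss. Section 2.8 (Data Collection) plans full data collection for dropouts who can be reached, and Section 2.11.1 says that dropouts available for the posttest will still be interviewed.

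**The concern.** An EM fill-in replaces each missing posttest with a value predicted from the observed data. A test run on the completed file makes two errors. It counts imputed participants as if they carried full information, and it sees too little spread, because predicted values lie on the regression line. Standard errors are then too small.

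That applies if group is a predictor in the EM model. If group is left out, imputed values in both arms are drawn to one pooled line. The test then keeps its level, but the group difference is diluted.

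The two errors act in different directions. The first can make the sensitivity analysis appear to confirm a per-protocol result that is due to chance. The second can make it appear to contradict a real one. The article does not say which model is used, so a reader of the results could not tell which error to expect.

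**Working it through.** **Inputs.** From Section 2.7: 80 enrolled per arm, 35% dropout, 52 per arm at posttest, d = 0.55, two-sided alpha 0.05. From Section 2.11.1: EM imputation, then time × group mixed ANOVA, which with two time points equals a t test on change scores. Assumed, because the article gives no value: pre-post correlation r = 0.5 (range 0.3 to 0.7), baseline and posttest SD of 1, posttests missing completely at random, equally in both arms.

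**The plan's own figure.** 52 / (1 − 0.35) = 80 per arm, so the dropout step reproduces. At the ceiling, 28 of 80 posttests per arm would be imputed. (Separately, 52 per group does not match the stated 90%. 2 × (1.960 + 1.282)² / 0.55² gives 70, whereas 80% power gives 2 × (1.960 + 0.842)² / 0.55² = 51.9, or 52. That does not affect this point.)

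**Group in the EM model.** Let n = 80 and let q be the observed fraction. The mean change in one arm then has approximately

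- true variance: (1 − r)²/n + (1 − r²)/(qn)
- variance as the test sees it: [(1 − r)² + q(1 − r²)]/n

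At 35% missing and r = 0.5:

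- true: 0.25/80 + 0.75/52 = 0.01755
- seen: (0.25 + 0.65 × 0.75)/80 = 0.00922
- ratio 1.904, square root 1.380

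The nominal cut-off of 1.96 therefore acts as 1.96/1.380 = 1.42, a two-sided error of about 15.5%. Simulation (20,000 trials per cell) gave 15.9%. The same formula gives 13.8% at r = 0.3 and 17.4% at r = 0.7; simulation gave 14.0% and 17.3%.

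**Group omitted.** Imputed participants contribute no group difference, so the expected estimate is q × 0.55. At 35% missing this is 0.65 × 0.55 = 0.3575 (simulated 0.357), and at 20% it is 0.80 × 0.55 = 0.44 (simulated 0.439). This does not depend on r. Simulated type I error stayed at about 5%.

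**Range of missingness, r = 0.5:**

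| Posttests missing | Type I error, group in model: formula | Simulation | Estimate of a true 0.55, group omitted (simulation) |
|---|---|---|---|
| 5% | 5.9% | 6.0% | 0.523 |
| 10% | 7.0% | 7.0% | 0.496 |
| 20% | 9.7% | 9.5% | 0.439 |
| 35% | 15.5% | 15.9% | 0.357 |

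**Does adding a random residual rescue it?** No. With group in the model, one imputation and a residual added, simulated type I error at 35% missing was 12.1% to 13.9% for r from 0.3 to 0.7.

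**Checks.** Complete-case analysis in the same simulations kept type I error at 4.7% to 5.1% at 35% missing, with a mean effect of 0.55. A separate simulation of multiple imputation (20 imputations, Rubin's rules, r = 0.5) gave 5.0% with an effect of 0.54 at 35% missing, and 5.5% at 20% missing.

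**The case against.** The strongest case against the point concerns its reach, and most of it stands.

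- **Analysis set.** Per protocol is primary. A per-protocol set without dropouts would probably contain few imputed posttests. A reader might infer that the trial's primary test runs at three times its nominal level; the documents do not support that. The article does not confine imputation to intention to treat, but nothing in it shows a material effect on the primary test.
- **Amount missing.** The 35% is a cautious planning figure for dropout, and posttests are sought from dropouts. It is a fair ceiling, not an expected rate, so the lower rows of the table are also plausible.
- **Other safeguards.** A reader might take intention to treat to be the only check on the primary result. Section 2.11.1 also plans regression for confounders and, if the groups differ, methods such as propensity score matching. Those address baseline imbalance rather than the exclusion of dropouts, but they mean the conclusion does not rest on one check.
- **Unequal harms.** With group omitted, the test keeps its level and errs towards no effect. That version would not falsely confirm a positive result.
- **Unstated detail.** That a single data set is meant is an inference, though the ordinary one when no pooling is named. The article does not say whether EM is for skipped questionnaire items or for whole missing posttests; the figures above concern the latter. An imputation model is commonly left to an analysis plan.

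The last objection does not remove the point. The article positively names a method, and every single-imputation version examined here either inflates type I error or dilutes the effect.

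**Conclusion.** The point holds as a should-fix weakness, mainly in the intention-to-treat sensitivity analysis. With group in the EM model, type I error rises from 5% to about 6%, 7%, 10% and 16% at 5%, 10%, 20% and 35% missing posttests (about 14% to 17% at 35% for correlations from 0.3 to 0.7). With group omitted, the level is kept but the effect shrinks by about the missing fraction.

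This rests on reading EM imputation as a single completed data set, on imputation of whole missing posttests, on an assumed pre-post correlation for the inflation (not for the shrinkage), and on equal missingness completely at random in both arms. A threefold error rate or a loss of a third of the effect describes the 35% ceiling only, and neither figure should be carried over to the primary per-protocol test.

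**What to change.** In Section 2.11.1, replace EM imputation of missing posttests with one of two methods:

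1. A likelihood-based linear mixed model (SPSS MIXED) fitted to all observed t0 and t1 values, without imputation.
2. Multiple imputation pooled by Rubin's rules, with arm, baseline outcome, age, sex, nationality and cycle in the imputation model.

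Attendance should not be an ordinary covariate in a model pooled across arms, because controls have no sessions before t1. It can be used only if imputation is done separately by arm, and then only within the intervention arm.

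The text should also state which analysis sets the method serves. The cost is a change of wording, slightly more analysis work in the software already planned, and confidence intervals that are wider but valid. No new data or participants are needed.

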### 2.2. Trial Outcomes and Hypothesis

#### 2.2.1. Primary Outcome

Psychological well-being is being measured with the WEMWBS [44]. The participants in the intervention group (IG) are expected to benefit significantly more in terms of their psychological well-being than adolescents assigned to the control group (CG; effect size of Cohen’s d ≥ 0.55).

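### Per protocol is the primary analysis of a superiority trial with an effectiveness aim, so adherence-based exclusion, possible only in the climbing arm, enters the headline comparison

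*Protocol article*

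**What the plan says.** Section 2.11.1 (Quantitative Data) fixes the order of the two analyses. "The primary data analytic strategy will be “per protocol" names the primary one, and the other follows: "As a sensitivity analysis, an additional analysis with “intention to treat” will be performed". The article gives no reason for this order and does not state what makes a participant per protocol.

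The question the trial sets itself is wider. Section 2.1 says "The aim of the study is to test the effectiveness of a climbing intervention among adolescent locals and refugees". Section 2.2.1 states a superiority hypothesis in terms of assignment: intervention participants are "expected to benefit significantly more in terms of their psychological well-being than adolescents assigned to the control group", with d of at least 0.55. The Discussion counts the naturalistic setting and the pragmatic evaluation of a real-world programme among the study's strengths.

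Four other places bear on the point:

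- Section 2.5 (Intervention): the control group has no climbing sessions until after the posttest.
- Section 2.7 (Sample Size Estimation): "we assumed a drop-out rate of 35% per intervention cycle". This takes 80 enrolled to 52 analysed in each arm. The set is labelled differently here: "This resulted in a necessary sample (as treated AT", followed by 52 members per group.
- Section 2.8 (Data Collection): "Complete data collection is also planned for dropouts, if available".
- Section 2.6 (Allocation): about 20% of eligible applicants choose their timing, and so their arm. The rest are allocated at random.

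**The concern.** A per-protocol comparison asks how those who followed the programme fared. An effectiveness aim asks what offering the programme does for those who were to receive it. In a superiority trial these two answers can differ, and the per-protocol answer is open to bias because membership of the set is decided after allocation.

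Here the decision falls on one arm. A waiting adolescent has nothing to adhere to before the posttest, whereas a climbing participant can miss sessions or give up. If those who stop climbing would have changed differently in well-being from those who continue, for reasons that have nothing to do with climbing, removing them shifts the intervention mean and leaves the control mean where it was. The balance that random allocation gave to most of the sample is lost to the same extent.

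The outcome is self-reported and unblinded, and enthusiasm for the programme may go with a better report of well-being. The likely direction is therefore in favour of the intervention. At stake is the headline result: its estimate, and the error rate of its test.

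**Working it through.** **1. The plan's own sample-size figures.** Inputs from section 2.7: two-sided alpha 0.05, d = 0.55, 35% dropout, and a stated beta of 90%, read as 90% power.

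- Dropout step: 52 / (1 − 0.35) = 80 per arm. This reproduces, and 80 × 0.65 = 52 is applied to both arms.
- The 52 itself does not reproduce at 90% power. A two-sample t test needs 71 per arm (70 by the normal approximation), and 52 per arm gives about 79% to 80% power. That is a separate matter and does not affect this point, but it means power has to be restated in any case.

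**2. Where selection can act.**

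| Kind of loss | Intervention group | Control group |
|---|---|---|
| No posttest | yes, 35% assumed | yes, 35% assumed |
| Posttest taken, sessions not followed | possible | not possible before posttest |

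Only the second row is asymmetric. The article gives no figure for it: 35% is a dropout rate, not a rate of per-protocol exclusion.

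**3. What a given bias would do to the test (the bias is an assumption).** With two groups and two time points, the time × group term of the mixed ANOVA is equivalent to a two-sample t test on change. The spurious difference b must therefore be a difference in change, in SD units of change. A stable difference in level, equal at t0 and t1, would cancel.

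With no true effect and 52 per arm, df = 102, the critical value is 1.983 and the noncentrality is b × √(52/2) = b × 5.099.

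| b (SD) | Share of 0.55 | Noncentrality | Two-sided rejection |
|---|---|---|---|
| 0 | 0% | 0 | 5.0% |
| 0.10 | 18% | 0.51 | 8.0% |
| 0.175 | 32% | 0.89 | 14.3% |
| 0.25 | 45% | 1.27 | 24.3% |

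The row 0.175 arises, for example, if 35% of the intervention group were excluded and would have changed by 0.5 SD less than those kept: 0.35 × 0.5 = 0.175. Both numbers in that product are assumptions. If the control group lost nobody (52 against 80), the last three rejection rates would be 8.6%, 16.4% and 28.6%.

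**4. What the wider set does to power (the share f is an assumption).** If dropouts receive a share f of the effect, the expected effect among all allocated is d × (0.65 + 0.35f). With 80 per arm, all measured, two-sided 0.05:

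| f | Expected d | Power at 80 per arm | Per arm for 90% |
|---|---|---|---|
| 0 | 0.55 × 0.65 = 0.36 | 61% | 166 |
| 0.5 | 0.55 × 0.825 = 0.45 | 81% | 104 |
| 1 | 0.55 | 93% | 71 |

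Missing posttests would lower these powers further.

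**The case against.** The strongest replies are these.

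- **The waiters are selected too.** This stands for retention: section 2.7 applies the same 35% loss to both arms. A reader might infer that selected attenders are compared with unselected waiters, but the documents do not support that. What remains is selection on adherence, which the control group cannot undergo.
- **The 35% is not an exclusion rate, and the per-protocol criteria are not shown.** This stands. They may be in a fuller document, so no size of bias can be read off the article. If the set meant only having a posttest, the rule would act in both arms. But the plan provides for dropouts who do take a posttest, and those are the participants on whom a per-protocol and an intention-to-treat analysis would be expected to differ.
- **The direction is not established.** This stands as a matter of proof. The obstacles the article names are exams, family accompaniment and the political and economic situation, none clearly tied to change in well-being. A bias in favour of climbing is plausible, not shown.
- **Intention to treat is planned anyway, and about 20% choose their arm.** Both are true. A sensitivity analysis would reveal a discrepancy, but the headline would still rest on the more exposed comparison. Self-selection is not removed by intention to treat; per protocol adds a second selection to it. Propensity methods are to be used only if important sociodemographic variables differ significantly, and need not capture motivation.

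A reader might also infer that three analysis sets leave room to choose the favourable one. The article plans two, in a fixed order. The as-treated label appears once, in the sample-size section, and is a mismatch of names.

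**Conclusion.** The point holds. The choice is stated outright, so it is not a detail left to a document not shown, and it does not fit the stated aim or hypothesis. It adds selection after allocation, in one arm, to the primary comparison.

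The size and direction of the resulting bias cannot be derived from the documents. The range of about 8% to 24% false rejection rests on an assumed spurious difference in change of 0.10 to 0.25 SD, with no true effect and 52 per arm. It shows that a bias well below the planned effect would matter; it does not estimate the bias in this trial. The mismatch between the as-treated label in section 2.7 and the per-protocol set in section 2.11.1 is minor, and is settled by the same correction.

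**What to change.** - In section 2.11.1, make primary the analysis of all participants in the group to which they were allocated or which they chose. Use every posttest value, including those already planned from dropouts, with a valid method for missing data.
- Report per protocol as a supporting analysis.
- In section 2.7, replace the as-treated label with the same primary set and restate the power for it.

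Both analyses and the posttests of dropouts are already planned, so no new kind of data is needed. The cost is a less favourable power statement: with 80 per arm all measured, about 61% if dropouts receive none of the effect, 81% if half and 93% if all. Recruitment is listed as complete in Table 1, so the lower figures may have to be reported as they are. The change does not remove the self-selection of the roughly 20% who choose their timing; that still needs adjustment and should be stated as a limitation.
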